**Figure 1 F1:**
[figure not shown]
Trial profile. LHW, Lady Health Worker, PO, Pulse Oximetry.

The primary outcome is hospital referral acceptance in children under 5 with severe pneumonia and to identify demographic and clinical predictors of hospital referral acceptance. The predictors will include distance of child home to referral facility, socioeconomic status of household, parental education, child age, nutritional status, respiratory rate, temperature, hypoxaemia and presence of other illnesses.

Secondary outcomes include duration of oxygen therapy, treatment failure, duration of hospital stay, vital and health status of child at day 7th and 14th.

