## Methods

### Study aims and design

The overall aim of the study is to assess if detection of hypoxaemia, and/or severe pneumonia in children 0–59 months by LHWs during their monthly home visits will increase hospital referral acceptance among families in district Jamshoro, Sindh, Pakistan.

Primary objectives are:

To assess and compare the impact of ‘pulse oximetry’ used by LHWs at household level on increasing hospital referral acceptance rates in intervention clusters (district Jamshoro) for children aged 0–59 months with severe pneumonia with the impact of LHWs using clinical signs alone in non-intervention clusters of the same district.To investigate the likely predictors (demographic, clinical) of hospital referral acceptance in both the groups.

Secondary objective is:

To compare clinical outcomes (treatment completion, treatment failure, hypoxaemia) of children 0–59 months who accepted referral to those who refused admission and were treated at home.

A community-based cluster randomised trial will be conducted in district Jamshoro, among children of ages 0–59 months (figure 1). In intervention areas, all children with cough, fever or difficulty in breathing (acute respiratory illness) will be assessed for study eligibility (signs and symptoms of severe pneumonia, or hypoxaemia alone, or severe pneumonia with hypoxaemia) by LHWs during their monthly home visit in their catchment area. In control areas, study eligibility will require detection of signs of severe pneumonia alone (online supplemental appendix 1) during LHW monthly visits. Data will be collected on demographics, likely predictors and clinical outcomes using a structured questionnaire.

10.1136/bmjopen-2020-046158.supp1Supplementary data

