### Sample size

Defining a cluster as (the catchment area of) one LHW, and assuming a power of 90% in detecting 50% increase in referral acceptance from a 10% baseline to 15% among children aged 0–59 months with severe pneumonia (pneumonia prevalence at 2-week recall (MICS Sindh): 7.5% (18% of which is assumed severe pneumonia) with ICC 0.001736. We need to capture a total of 4160 children with severe pneumonia in both intervention and control groups.

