### Data analysis

The primary analysis for each outcome will perform on an ‘intention-to-treat’ basis, that is, all children included in the analysis who were enrolled in the study according to the group to which they were allocated. All analyses will account for the cluster randomised design to ensure correct type I error rates and CIs.^35^ Baseline characteristics will be compared by analysing differences in means and proportions among the study arms. Categorical outcomes will be compared using χ^2^ test and continuous outcomes using Student’s t-test. For analysis of predictors of referral acceptance, generalised linear model will be used with logit link function. The univariate analysis will be conducted to explore the independent effect of each predictor on outcome. The variables significant at a liberal p<0.20 will be included in multivariate model for adjustment. The results will be reported as relative risk with 95% CI. Type 1 error will be set at 5% level. All analysis will be done using STATA V.15.

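### Identifying nine observational predictors shares primary status with the randomised comparison, and the predictors are chosen by a p<0.20 screen that leaves post-selection bias in their intervals

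*Protocol article*

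**What the plan says.** The Study aims and design section lists two primary objectives. The first is the randomised comparison of referral acceptance between pulse oximetry clusters and clinical-signs clusters. The second is "To investigate the likely predictors (demographic, clinical) of hospital referral acceptance in both the groups". The outcome paragraph after Figure 1 repeats the pairing: "The primary outcome is hospital referral acceptance in children under 5 with severe pneumonia and to identify demographic and clinical predictors of hospital referral acceptance". It names nine predictors: "distance of child home to referral facility, socioeconomic status of household, parental education, child age, nutritional status", followed by "respiratory rate, temperature, hypoxaemia and presence of other illnesses". Both places also have a secondary tier, and the predictors are not in it.

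The Data analysis section specifies a generalised linear model with logit link for the predictors. Of the first step it says: "The univariate analysis will be conducted to explore the independent effect of each predictor on outcome". Then: "The variables significant at a liberal p<0.20 will be included in multivariate model for adjustment". Results are to be relative risks with 95% confidence intervals, and all analyses are to account for clustering. On error it says only: "Type 1 error will be set at 5% level".

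The Sample size section is built on one contrast, 10% versus 15% referral acceptance with 90% power, and gives a total of 4,160 children.

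**The concern.** Identifying predictors is an analysis aim, not an outcome, and the sentence that defines the primary outcome merges the two. One of the two primary aims is randomised and sized. The other is observational, covers nine variables and has no sample size behind it. As worded, an association between, say, temperature and acceptance could be reported as a primary finding alongside the randomised result.

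The screen adds a second problem. A variable reaches the adjusted model only if it already looked associated with acceptance in the same children. A nominal 95% interval takes no account of that selection, so for retained variables it is biased away from no association.

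**Working it through.** **Plan's own figure.** The article states no error rate for the set of primary tests, so there is none to reproduce. The planning figure used below is 4,160. The usual pooled two-proportion formula (10% v 15%, two-sided 5%, 90% power) gives 918 per arm, or 1,836 in total. If all 188 clusters are used, there are 4,160/188 = 22.1 children per cluster and the design effect is 1 + (22.1 − 1) × 0.001736 = 1.037, giving about 1,903. So 4,160 does not follow from the stated inputs. That is a separate matter; here 4,160 enters only the count of acceptances in step 5.

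**Step 1, count the tests.** Five predictors in the first part of the list and four in the second make nine. With the arm comparison there are ten tests under a primary label, each at 5% (sidedness is not stated; two-sided assumed).

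**Step 2, reference values without the screen.** If all ten nulls are true and the tests are independent, 1 − 0.95^10 = 40.1%. For the nine predictors alone, 1 − 0.95^9 = 37.0%. If all ten test statistics had correlation 0.5, simulation gives 28.7%.

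**Step 3, the procedure as written.** Simulated trials had nine null predictors with a common correlation, a univariate p<0.20 screen, then a joint model at 5%, plus an independent arm test at 5%. Assumptions: 2,000 children, 12.5% acceptance, no clustering, a linear approximation to the logit model, and 4,000 trials per setting.

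| Predictor correlation (assumed) | Any predictor at 5% | Any predictor or the arm test |
|---|---|---|
| 0 | 36.2% | 39.0% |
| 0.1 | 34.8% | 37.7% |
| 0.2 | 29.9% | 33.4% |
| 0.3 | 22.4% | 26.2% |
| 0.5 | 10.0% | 15.0% |

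A separate simulation with a logit model (2,080 children, 2,000 trials per setting) gave 35.7%, 29.4% and 9.9% for the predictors at correlations 0, 0.2 and 0.5. Adding an independent arm test, 1 − (1 − 0.357) × 0.95 = 38.9%; the other two become 32.9% and 14.4%. The two simulations agree.

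**Step 4, what the screen does.** At correlation 0 the screened rate for nine predictors is 36.2%, against 37.0% unscreened, so the screen adds no false positives. Its effect is conditional. Of uncorrelated null predictors that pass at p<0.20, a fraction 0.05/0.20 = 25% also pass at 5%. In the logit simulation the figure was 24.5% at correlation 0, 21.6% at 0.2 and 7.6% at 0.5. Given retention, then, a nominal 95% interval for a null predictor misses the null more than 5% of the time.

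**Step 5, is selection needed?** At planning rates, acceptances number 2,080 × 0.10 + 2,080 × 0.15 = 208 + 312 = 520, or 520/8 = 65 for each of eight predictors. The Study status section reports 235 + 184 = 419 children enrolled by October 2020. At 12.5% acceptance that is about 52 events, or 6.5 per predictor.

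**Step 6, can all nine be modelled in both arms?** Under Participant, Intervention delivery and the control-arm section, health workers measure oxygen saturation only in intervention clusters. Under Procedure at referral facility, the next stated oximetry is in children who reach hospital. As described, control families who refuse referral have no saturation reading at the enrolment visit. Hypoxaemia therefore cannot enter a pooled model as a pre-referral predictor.

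**The case against.** The strongest reply is that the article leaves no doubt about its main question. The overall aim, the sample size and the follow-on work described under Limitations all concern the effect of oximetry on referral acceptance. The predictor work is worded as investigating and exploring. A hierarchy or multiplicity rule may sit in a full protocol or analysis plan that is not shown, so its absence here is not a fault. The global null is also doubtful, since the Introduction itself names distance and lack of money as reasons for delay.

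Much of this stands, and it rules out several stronger readings.

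- A reader might infer that the primary false-positive rate is 29% to 40% instead of 5%. Those figures are for ten unscreened tests, not the written two-step rule, and the article does not promise 5% for the whole set.
- A reader might infer that a predictor could make the trial positive when oximetry does nothing. No stated rule says so.
- A reader might infer that the arm test is compromised. It is one test at 5%.
- A reader might infer that the screen multiplies false positives. Step 4 shows that it does not.

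If distance and socioeconomic status are truly associated with acceptance, eight null tests remain. Unscreened and independent, they give 1 − 0.95^8 = 33.7%, so the doubt about the global null lowers the figure without removing the issue.

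The reply does not answer the wording itself. The predictor aim is expressly placed among the primary objectives and inside the primary outcome. The word explore is attached only to the univariate step. The screen is a stated rule, not an open detail.

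**Conclusion.** The point holds as one of labelling and of analysis method. The protocol gives primary status to nine observational associations alongside the single contrast it was randomised and sized for, and it fixes a data-driven selection rule whose reported intervals make no stated allowance for that selection. The randomised comparison, taken alone, is unaffected.

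The 15% to 39% in step 3 rests on a global null, an assumed common predictor correlation of 0.5 to 0, and an arm test independent of the predictors. It counts hypoxaemia as one of the nine tests, although it can be examined before referral only in the intervention arm. The figure measures how readily something in the primary set would look positive by chance; it is not the error rate of the trial's conclusion about oximetry. The correction should be made before analysis, which is feasible because data collection was still in progress when the article was written.

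**What to change.** 1. In the objectives and the outcome paragraph, name the between-arm comparison of hospital referral acceptance as the sole primary contrast, tested at 5%. Move the predictor aim to a secondary or exploratory objective, reported as estimates with 95% confidence intervals.
2. In the Data analysis section, delete the p<0.20 screen. Enter the eight listed predictors other than hypoxaemia, as measured before referral in both arms, in one prespecified model that allows for clustering.
3. Analyse hypoxaemia as a predictor in the intervention arm only, and say why.
4. State in advance what happens if enrolment falls well short of 4,160. The predictor list should then be shortened by a prespecified rule that does not look at the outcome.

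The cost is a change of wording in three places, with no additional children or data. The small downside is that predictor results can no longer be presented as primary findings.

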**Methods and analysis:**

A cluster randomised controlled trial using pulse oximetry as intervention for children with severe pneumonia will be conducted in community settings. Children aged 0–59 months with signs of severe pneumonia will be recruited by LHWs during routine visits in both intervention and control arms after consent. Severe pneumonia will be defined as fast breathing and/or chest in-drawing, and, one or more danger sign and/or hypoxaemia (Sa02 <92%) in PO (intervention) group and fast breathing and/or chest in-drawing and one or more danger sign in clinical signs (control) group. Recruits in both groups will receive a stat dose of oral amoxicillin and referral to designated tertiary health facility. Analysis of variance will be used to compare baseline referral acceptance in both groups with that at end of study.

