This study recognises the LHW as a powerful conduit for reaching under 5 children at household level and identifying severe pneumonia in under five at an early stage. It also recognises the underestimation of hypoxaemia (arterial oxygen saturation, SpO_2_ of <90%), a major risk factor for pneumonia mortality at community level and assesses its prevalence. The reported prevalence of hypoxaemia in under 5 acutely ill children is 5%–58% in facilities^13–16^ and 16%–39% in community settings.^17^ A 4.3-time higher risk of mortality has been associated with pneumonia with hypoxaemia than in children with pneumonia without hypoxaemia.^13^ Hypoxaemia is also predictive of treatment failure with amoxicillin in children aged 3–59 months.^18^ In resource-poor settings where pulse oximetry is not feasible, signs and symptoms of severe pneumonia (sleepiness, cyanosis, head nodding/grunting and inability to move) are used as predictors of hypoxaemia. However, the validity of clinical signs to predict hypoxaemia varies and it is often difficult for physicians working in settings, where objective detection of hypoxaemia is not available, to decide whether the child coming with severe pneumonia requires administration of oxygen or not.^15 19 20^

Pulse oximetry^16^ is a rapid, portable, non-invasive and accurate method of measuring Sp02 and has therefore been used in trial and clinical settings to detect hypoxaemia. Appropriate oxygen therapy (based on PO findings rather than clinical signs of severity alone) has been associated with lower mortality risk.^19^ Assuming access to supplemental oxygen, PO could potentially avert up to 148 000 severe pneumonia-related deaths if implemented, and, combining PO with IMCI assessment for pneumonia has been shown to be cost-effective in 15 high burden countries.^21^ Emdin *et al* found first level LHWs in periurban Karachi could easily perform pulse oximetry on young infants on well and sick visits to a primary healthcare facility.^22^

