### Participant

Any child aged 0–59 months having signs and symptoms of acute respiratory illness (cough, fever, difficulty in breathing) in intervention clusters will undergo assessment of (1) signs and symptoms of severe pneumonia and (2) pulse oximetry during monthly LHW home visits. Presence of severe pneumonia with or without hypoxaemia, or hypoxaemia alone will merit hospital referral (non-facilitated). Any child aged 0–59 months having signs and symptoms of acute respiratory illness (cough, fever, difficulty in breathing) in control clusters will undergo assessment of (1) signs and symptoms of severe pneumonia alone. Presence of severe pneumonia will merit hospital referral (non-facilitated). Exclusion criteria will include lack of consent and, non-availability (lost to follow-up, migration) on days of scheduled follow-up visits (days 7 and 14). Those who accepted referral but did not show up at hospital will be included in final analysis.

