### Participant recruitment and study procedures

#### Intervention delivery

Children aged 0–59 months with cough and/or difficult breathing during regular home visits of LHWs will be assessed for first, signs and symptoms of severe pneumonia (fast breathing/chest in-drawing and one or more danger sign (unable to eat/drink, vomiting, convulsion and lethargy/unconsciousness) and/or stridor)) and second, hypoxaemia (SpO2 <92%) using a handheld pulse oximeter (Masimo Rad-5v) to measure blood oxygen saturation level. LHWs will also do case management of children with pneumonia and severe pneumonia. A 3-day course of oral amoxicillin will be given to children with pneumonia at home, whereas children meeting referral criteria (severe pneumonia alone, hypoxaemia alone or severe pneumonia and hypoxaemia) after obtaining informed consent (online supplemental appendix 2), will be administered a stat dose of oral amoxicillin and referred to nearest referral hospital (DHQ Kotri).

The study investigators will have provided these pulse oximeters to the LHW programme in advance and highlighted which ones will receive them. Physicians at the referral centre serving the intervention clusters will also receive handheld pulse oximeters. All the LHWs and staff will be trained on the use, and maintenance of these pulse oximeters. Children with severe pneumonia with or without hypoxaemia will be advised to go to hospital for antibiotics and oxygen, using the PO reading as a tool to convince parents. Children with hypoxaemia alone, without signs of severe pneumonia, will be referred to hospital to rule out cyanotic congenital heart disease. Name of the predesignated health facility with available oxygen and study physician will be provided to all the LHWs so that Study Workers (non-LHW study personnel) can coordinate with study physicians and ensure the patient has reached and is receiving safe and recommended care at referral facility. Project staff will pretest and regularly monitor PO accuracy and quality of readings.

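### The predictor analysis as written confounds hypoxaemia with clinical severity, because an intervention child without hypoxaemia can enrol only with severe signs

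*Protocol article*

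**What the plan says.** **Entry, intervention arm.** Study aims and design admits children with "signs and symptoms of severe pneumonia, or hypoxaemia alone, or severe pneumonia with hypoxaemia". Participant and Intervention delivery repeat this for referral. Intervention delivery adds: "Children with hypoxaemia alone, without signs of severe pneumonia, will be referred to hospital to rule out cyanotic congenital heart disease".

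**Entry, control arm.** "In control areas, study eligibility will require detection of signs of severe pneumonia alone".

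**Entry, abstract.** Methods and analysis is narrower. It requires fast breathing and/or chest in-drawing of every child, together with "one or more danger sign and/or hypoxaemia (Sa02 <92%) in PO (intervention) group". Here hypoxaemia can stand in for the danger sign but not for the respiratory sign.

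**Predictors.** Identifying likely demographic and clinical predictors of acceptance is the second primary objective. The list given after Figure 1 includes "parental education, child age, nutritional status, respiratory rate, temperature, hypoxaemia and presence of other illnesses". Danger signs, severity class and entry route are not named.

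**Model.** Data analysis states: "The univariate analysis will be conducted to explore the independent effect of each predictor on outcome". Variables with p<0.20 then go into a multivariable generalised linear model with a logit link.

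**The concern.** Write S for severe clinical signs and H for hypoxaemia. Of the four S-by-H combinations, the one with neither cannot enrol in the intervention arm. The H-negative comparison group is then entirely S-positive, while the H-positive group mixes children with and without signs. Among enrolled children this produces a negative dependence between H and S that comes from the entry rule and need not exist in the community.

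If S itself affects whether families go to hospital, the crude contrast for H carries part of the effect of S. The univariate result, described in the plan as an independent effect, would not be one. Because entry to the multivariable model depends on that result, hypoxaemia could also be dropped before any adjustment is made.

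Hypoxaemia is the finding that the oximeter adds to clinical assessment, so a misleading coefficient for it would weaken the explanation of any trial result. The point concerns the predictor objective only and does not bear on the comparison between arms.

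**Working it through.** There is no stated figure to reproduce, because the plan gives no expected effect for hypoxaemia. The check has a structural part, which needs no numbers, and an illustration, which needs assumed ones. It is confined to the intervention arm, where SpO2 is measured at home.

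**1. Structure**

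| Combination | Broad rule (Study aims and design, Participant, Intervention delivery) | Abstract rule, given fast breathing or in-drawing (S = danger sign) |
|---|---|---|
| S yes, H no | enrolled | enrolled |
| S yes, H yes | enrolled | enrolled |
| S no, H yes | enrolled | enrolled |
| S no, H no | not enrolled | not enrolled |

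Under either rule, all H-negative enrolled children have S.

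**2. Illustration: inputs**

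- Acceptance 10% at S yes, H no. This borrows the Sample size baseline.
- P(S) = 18% of screened children. Sample size gives 18% as the severe share of pneumonia; applying it to screened children is an assumption.
- Assumed: scenario A, P(H|S) = 30% and P(H|no S) = 5%; scenario B, 20% and 10%.
- Assumed: odds ratio for H of 1.5; odds ratio for S of 0.7, 1, 2 or 3.

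**3. Cell shares of screened children**

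- A: S and H 0.18×0.30 = 0.054; H alone 0.82×0.05 = 0.041; S only 0.18×0.70 = 0.126.
- B: 0.18×0.20 = 0.036; 0.82×0.10 = 0.082; 0.18×0.80 = 0.144.

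**4. Acceptance by cell**

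- S only: odds 1/9, risk 0.100.
- S and H: odds 1.5/9 = 0.1667, risk 0.1429. The true risk ratio for H among children with signs is 1.43.
- H alone: odds 0.1667/OR_S. Risk is 0.1429 (OR_S = 1), 0.0769 (OR_S = 2), 0.0526 (OR_S = 3) and 0.1923 (OR_S = 0.7).

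**5. Crude risk ratio among enrolled children**

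RR = [share(S and H)×0.1429 + share(H alone)×risk(H alone)] / [share(S and H) + share(H alone)] / 0.10

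Example, A with OR_S = 2: (0.054×0.1429 + 0.041×0.0769)/0.095 = 0.1144, so RR = 1.14.

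| OR_S | True RR within S | Crude RR, A | Crude RR, B |
|---|---|---|---|
| 1 | 1.43 | 1.43 | 1.43 |
| 2 | 1.43 | 1.14 | 0.97 |
| 3 | 1.43 | 1.04 | 0.80 |
| 0.7 | 1.43 | 1.64 | 1.77 |

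The direction follows the sign of the S effect.

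**6. Does adjustment help?** In 2,000,000 simulated children (scenario A), the crude odds ratio for H was 1.50, 1.17 and 1.05 for OR_S of 1, 2 and 3. With S in the logit model it was 1.51, 1.52 and 1.50, against a true 1.5. With three occupied cells, the adjusted H coefficient is in effect the contrast among children with signs. The effect of hypoxaemia in children without signs cannot be estimated from enrolled children.

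**7. The p<0.20 screen.** Take 2080 intervention children (half of 4160), scenario A, a normal approximation and no clustering. The H-negative group is 2080×0.126/0.221 = 1186, and the H-positive group 2080×0.095/0.221 = 894, of whom 2080×0.054/0.221 = 508 have signs.

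- Crude, OR_S = 2: z = (0.1144−0.100)/√(0.1144×0.8856/894 + 0.09/1186) = 1.05. The probability of passing is Φ(1.05−1.28) + Φ(−1.05−1.28) ≈ 0.42.
- Crude, OR_S = 3 (risk 0.1039): z = 0.29, probability about 0.22.
- Children with signs only: z = (0.1429−0.100)/√(0.1429×0.8571/508 + 0.09/1186) = 2.41, probability about 0.87.

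**The case against.** **The predictor list need not be exhaustive.** The article says what the predictors will include, and the objective speaks of clinical predictors generally. A fuller protocol or SAP may add danger signs. This stands in part: a reader might infer that the multivariable model cannot remove the problem, and that is too strong, because adding a sign indicator recovers the effect. It does not rescue the univariate step, and a p<0.20 rule does not ensure that hypoxaemia or the sign term reaches the model.

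**The direction is not established.** This stands. A reader might infer that the hypoxaemia effect must be biased towards or past the null. That requires severe signs to raise acceptance. The Introduction supports this only qualitatively, by naming failure to recognise seriousness as a reason for delay.

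**The figures that might size it do not fit.** This also stands. The Introduction's 16%–39% community prevalence is for acutely ill children, not children with severe signs, and that section defines hypoxaemia as SpO2 below 90% while enrolment uses below 92%. Study status reports 235 and 184 enrolled, but nothing says that the 51 extra children entered on hypoxaemia alone.

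**The entry definition is itself inconsistent.** Under the abstract, hypoxaemic children still need fast breathing or in-drawing, so it would be wrong to say that they need no clinical sign. Listing respiratory rate might also capture part of severity. The confounding then runs through danger signs, which are not listed.

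**Conclusion.** The point holds in conditional form. It is certain from the entry rules that enrolled intervention children without hypoxaemia all have severe signs (danger signs, under the abstract), while hypoxaemic children need not. The stated univariate contrast for hypoxaemia is therefore confounded with clinical severity whenever signs affect acceptance and some children enrol on hypoxaemia without those signs. The planned screen can carry that distortion into the choice of model.

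The effect is likely attenuated, and possibly reversed, if signs raise acceptance. It is unbiased if signs have no effect and inflated if they lower acceptance. Crude risk ratios of 0.80 to 1.77 against a true 1.43 are illustrations under assumed prevalences and odds ratios, not estimates for this trial.

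A reader might also infer that the trial's hypoxaemia prevalence will be inflated. The Introduction calls hypoxaemia "a major risk factor for pneumonia mortality at community level and assesses its prevalence", but no section says that prevalence will be computed from enrolled children. Oximetry is planned for all intervention children with respiratory illness and LHWs complete a screening form, so a screened-child denominator may exist. No error is shown there.

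**What to change.** In Data analysis, specify one of the following for the hypoxaemia predictor:

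1. Estimate it only among children who meet the clinical-sign definition in the section on the active control (clinical signs assessment).
2. Keep all enrolled intervention children and force a severe-sign or danger-sign indicator into the model, exempt from the p<0.20 rule.
3. Use a three-level entry route (signs only, signs with hypoxaemia, hypoxaemia alone) in place of the hypoxaemia term. It must not sit beside that term: in the intervention arm the route fully determines hypoxaemia, so the two are perfectly collinear.

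Under any option, report hypoxaemia-alone children separately, since Intervention delivery gives a different reason for their referral, and do not call the crude result an independent effect.

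Reconcile the entry definition in the abstract with those in Study aims and design, Participant and Intervention delivery, so that it is clear which sign indicator is needed.

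The cost is a change of wording. Option 1 also loses the hypoxaemia-alone children from the predictor model, a slight loss if they are few (0.041/0.221, about 19% of enrolled intervention children, in scenario A). Options 2 and 3 lose none. All options need signs and SpO2 recorded for each enrolled intervention child; the data forms are not shown, so this should be confirmed.
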